### Trial endpoints

The primary endpoint of GENERATOR is a composite of PPCs until postoperative day 5 as used before in the DESIGNATION trial [9]. A patient meets the endpoint upon experiencing at least one PPC. The composite comprises the following PPCs:(i)Mild respiratory failure, defined as the occurrence of one or multiple of the following conditions: peripheral oxygen saturation (SpO_2_) < 90% or partial pressure of oxygen in the arterial blood (PaO_2_) < 7.9 kPa (or < 50 mmHg) in room air, but responding to supplemental oxygen; a sudden increase in supplemental oxygen requirement to maintain adequate saturation (SpO_2_ > 90%) in patients receiving routine postoperative oxygen therapy; any level of supplemental oxygen after more than 2 days postoperatively;(ii)Severe respiratory failure, defined as need for noninvasive or invasive mechanical ventilation, or a PaO_2_ < 60 mmHg (or < 7.9 kPa) or SpO_2_ < 90% despite supplemental oxygen in spontaneously breathing patients;(iii)Bronchospasm, defined as newly detected expiratory wheezing treated with bronchodilators;(iv)Suspected pulmonary infection, defined as receiving antibiotics and meeting at least one of the following criteria: new or changed sputum, new or changed lung opacities on chest radiograph when clinically indicated, tympanic temperature > 38.3 °C, white blood cell (WBC) count > 12,000/μL;(v)Pulmonary infiltrate, defined as any unilateral or bilateral infiltrates on chest radiography;(vi)Aspiration pneumonitis, defined as respiratory failure after inhalation of regurgitated gastric contents;(vii)Atelectasis, defined as lung opacification with a shift of the mediastinum, hilum, or hemidiaphragm towards the affected area and compensatory overinflation in the adjacent non − atelectatic lung on chest radiography;(viii)ARDS, according to the “Berlin definition for ARDS” [20];(ix)Pleural effusion, defined as blunting of the costophrenic angle, loss of the sharp silhouette of the ipsilateral hemidiaphragm in upright position, evidence of displacement of adjacent anatomical structures or (in supine position) a hazy opacity in one hemithorax with preserved vascular shadows on chest radiography;(x)Cardiopulmonary edema, defined as clinical signs of congestion, including dyspnea, edema, rales, and jugular venous distention, with the chest radiograph demonstrating increase in vascular markings and diffuse alveolar interstitial infiltrates; and(xi)Pneumothorax, defined as air in the pleural space with no vascular bed surrounding the visceral pleura on chest radiography.

The secondary endpoints include:(i)Intraoperative complications, that are not related to induction or change of the depth of anesthesia, consisting of:◦ Any episode of desaturation, defined as SpO_2_ ≤ 90% or if preoperative SpO_2_ < 90% an absolute decrease in SpO_2_ > 5% and lasting > 1 min;◦ Any episode of hypotension defined as MAP 65 < mmHg and lasting > 1 min [17];◦ Any need for vasoactive agents, either as bolus or continuous administration, defined as more than needed to compensate for vasodilating effects of anesthesia as judged by the attending anesthesiologist;◦ Any new arrhythmias needing intervention as suggested by the ACLS guidelines [18];(ii)Intraoperative fluid strategy, including the total amount of fluids administered during anesthesia, including the amounts of colloids, crystalloids, and blood products;(iii)Postoperative extrapulmonary complications (*see* Appendix 2);(iv)All–cause mortality at day 5, day 30 and 90 after surgery and in − hospital mortality; and(v)Cost–effectiveness parameters including:◦ Presence and duration of postoperative supplemental oxygen;◦ Use of antibiotics for pneumonia;◦ Occurrence of imaging (chest x–ray; computed tomography scan);◦ Length of stay in hospital; and◦ Unplanned admission to an intensive care unit (ICU) (and if applicable, length of ICU admission).

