### Minimization of bias

The local investigators perform randomization using the randomization tool in Castor Electronic Data Capture (EDC) [19]. Included patients will be randomly allocated in a 1:1 ratio to the individualized high PEEP with RMs group or the standard low PEEP group without RMs. The allocation sequence is generated by Castor EDC, uses permuted blocks with a maximum block size of 6, and is stratified per center and by body mass index (≤ 30 vs. > 30 kg/m^2^). Further minimization of bias will be achieved by involving at least two independent investigators per site. One investigator will be responsible for the preoperative and intraoperative trial period. A second investigator, who will remain blinded for treatment allocation, will score the primary and secondary postoperative outcome measures. Inherently to the type of intervention, the attending anesthesiologist is not blinded. Other caregivers, including the surgeon, research staff and ward nurses are blinded to treatment allocation.

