After induction of anesthesia, variables are collected hourly during the intraoperative period. These variables include ventilator settings, vital parameters, intra-abdominal pressure, administered fluids and vasoactive drugs, blood transfusions, need for rescue strategy for hypoxemia, intraoperative complications possibly related to PEEP titrations, preapproved protocol deviations and violations, details of anesthesia (type, epidural analgesia, neuromuscular function monitoring), patient positioning during surgery, arterial blood gas results (only if deemed necessary for clinical care for the patient), amount of fluid loss, and duration of both surgery and anesthesia procedures. Patients allocated to the individualized high PEEP with RMs group will have their plateau pressure recorded at the end of each decremental PEEP trial step and a ΔP–PEEP graph will be drawn.

Postoperatively, clinical data and the occurrence of pulmonary and extrapulmonary postoperative complications are collected. Blood tests and chest imaging will only be performed when considered necessary for the patients’ clinical care. Life status (death or alive) will be recorded during the first five postoperative days and at day 90 after surgery. Total length of stay in hospital, unplanned admission to an intensive care unit (ICU), and length of stay in the ICU are captured as well. To assess the health − related quality of life, the validated and commonly used EQ − 5D − 5L questionnaire will be sent out by email at day 90 after surgery to Dutch patients.

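### Intraoperative safety endpoints are filtered by judged cause with no blinded assessor described; for vasoactive agents the unblinded anesthesiologist decides

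*Protocol article*

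**What the plan says.** Trial endpoints, secondary endpoint (i), groups four intraoperative events under one qualifier, that they be events "that are not related to induction or change of the depth of anesthesia". No person, rule or time window is given for applying it.

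Within the group:
- Hypotension has a numeric criterion: "Any episode of hypotension defined as MAP 65 < mmHg and lasting > 1 min". The inequality sign is misplaced. Preapproved protocol deviations has it the expected way round, as MAP below 65 mmHg.
- Desaturation is an SpO2 of 90% or less or, if the preoperative value was below 90%, "an absolute decrease in SpO_2_ > 5% and lasting > 1 min".
- New arrhythmias count if they need intervention under a named guideline.
- Need for vasoactive agents is "defined as more than needed to compensate for vasodilating effects of anesthesia as judged by the attending anesthesiologist".

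Minimization of bias says that "the attending anesthesiologist is not blinded". It assigns one investigator to the preoperative and intraoperative period and a second, blinded one to the postoperative outcomes. The Discussion likewise claims full blinding only for patients and postoperative assessors.

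**The concern.** For vasoactive agents, the endpoint is itself an opinion on cause, and the person who holds it knows the allocation and delivers it. The same vasopressor dose could be put down to PEEP in one arm and to ordinary anesthetic vasodilation in the other, or the reverse. The qualifier over the whole group adds a second judgement of cause, with no blinded assessor described.

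Hemodynamic effects are a foreseeable harm of this intervention. Recruitment maneuvers raise PEEP to 20 cm H2O, controls stay at 5 cm H2O, and the list of permitted deviations provides for low blood pressure after PEEP titration. Statistical analysis tests every outcome two-sided at 5%, so a difference produced by attribution would carry a p-value. A real difference could equally be hidden.

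**Working it through.** **Step 1. Who can filter what**

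| Component | Criterion | Judge of cause named? | Blinded assessor described? |
|---|---|---|---|
| Vasoactive agents | Use beyond that explained by anesthesia | Yes, the attending anesthesiologist (unblinded) | No |
| Hypotension | MAP threshold, > 1 min | No | No |
| Desaturation | SpO2 threshold, > 1 min | No | No |
| New arrhythmia | Intervention per guideline | No | No |

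The first row is a stated rule: followed as written, it makes the outcome depend on an unblinded judgement. The other three have outside criteria but sit under the group qualifier, and the blinded investigator's remit does not reach them.

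**Step 2. How differential attribution acts**

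Let p be the true event rate, equal in both arms, and let f0 and f1 be the shares of events removed in the control and intervention arms.

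- Observed rates: p(1 − f0) and p(1 − f1)
- Observed risk ratio: (1 − f1)/(1 − f0)

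If f0 = f1, the ratio stays at 1 and events are only lost. Bias needs f0 and f1 to differ.

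**Step 3. Illustration**

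The documents give no rate for these endpoints and no removal share. Assumed: p = 0.30, 0.50 or 0.70; f0 = 0.20; f1 = 0.25 or 0.30. The only input from the plan is 860 per group (Sample size calculation). That figure reproduces for 30% versus 24% at 80% power with pooled variance:

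n = [1.96√(2 × 0.27 × 0.73) + 0.842√(0.30 × 0.70 + 0.24 × 0.76)]² / 0.06² ≈ 859.

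Chance of a spurious significant difference = Φ(z − 1.96), with z = difference / √(2p̄(1 − p̄)/860). Example with p = 0.30 and f1 = 0.25: rates 0.240 and 0.225, p̄ = 0.2325, standard error 0.0204, z = 0.74, Φ(−1.22) = 0.11.

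| True rate | f1 = 0.25: observed, control vs intervention | Chance | f1 = 0.30: observed, control vs intervention | Chance |
|---|---|---|---|---|
| 30% | 24.0% vs 22.5% | 11% | 24.0% vs 21.0% | 32% |
| 50% | 40.0% vs 37.5% | 19% | 40.0% vs 35.0% | 57% |
| 70% | 56.0% vs 52.5% | 31% | 56.0% vs 49.0% | 83% |

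The risk ratio is 0.75/0.80 = 0.94 in the first case and 0.70/0.80 = 0.875 in the second. Exchanging the shares between arms reverses the direction (1/0.9375 = 1.07 and 1/0.875 = 1.14). The table shows sensitivity to a gap of 5 to 10 percentage points. It does not estimate the gap in this trial.

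**The case against.** The strongest reply is that little here is open to opinion. The group qualifier excludes only events tied to induction or to a change in anesthetic depth. Induction precedes the first recruitment maneuver, which follows insufflation, so excluding it mostly removes noise. Hypotension and desaturation have numeric criteria. An unblinded anesthesiologist is unavoidable and is acknowledged in the Discussion. Fluids, vasoactive drugs and deviations are also recorded, and a monitoring board oversees safety.

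Much of this stands, and it rules out three stronger readings that a reader might infer:
- *That the anesthesiologist filters all four components.* This is plausible, but the text names that judge only for vasoactive agents.
- *That the filter could remove any event without limit.* It is confined to induction and change of depth.
- *That episodes longer than 1 minute are detected from hourly readings, so that a 1-minute episode is caught 1 time in 60 (1.7%).* Trial visits and data collection does say "After induction of anesthesia, variables are collected hourly during the intraoperative period". But that list also holds surgery duration and protocol deviations, which cannot be spot samples. The endpoint refers to any episode, and Handling of data names the electronic patient record as the source. Sparse sampling alone would also cost sensitivity in both arms and would not by itself favor one.

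The same list mentions complications possibly related to PEEP titration, which controls do not undergo. The documents do not say that this item feeds the secondary endpoint, so the point does not rest on it.

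The reply does not answer the vasoactive clause. Unavoidable unblinding is a reason to keep that clinician's opinion out of the outcome definition. The change-of-depth clause also remains a judgement with no blinded assessor.

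**Conclusion.** The point holds in a limited form. The vasoactive-agent endpoint is defined by an unblinded judgement of cause, and a further cause filter covers all intraoperative complications with no blinded assessment described. This is a stated rule that can bias the comparison, so it is more than detail left to a fuller document. Bias arises only if attribution differs by arm; neither its direction nor its size can be derived from the documents. The illustrated risk ratios of 0.94 and 0.875 rest wholly on the assumed removal shares and event rates. These are secondary endpoints, so the primary composite and the 1806-patient sample size are not touched. The change is worth making because the intraoperative harm comparison will be read alongside the primary result.

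**What to change.** Define the intraoperative endpoints in both arms by threshold and time:
- Count every episode meeting the existing MAP and SpO2 criteria for more than 1 minute, whatever its presumed cause. Correct the misplaced inequality sign.
- Use one window, from abdominal insufflation to the end of anesthesia, so that induction is excluded by time and not by opinion. Apply the same window to arrhythmias.
- Report vasoactive agents as administered in that window: any use, and dose where recorded.
- Keep the anesthesiologist's attribution as a descriptive supplement.

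The cost is endpoint wording and data extraction. Recruitment began in December 2023, so events already filtered out at entry would have to be recovered from patient records. The documents do not show that total dose is captured or that every site has an automated anesthesia record; some sites may rely on manual entry. Some anesthesia-related events will enter both arms and dilute the contrast. The intervention arm starts at a PEEP of 10 cm H2O, possibly before insufflation, so earlier events should be tabulated descriptively. Patient care does not change.

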### Trial visits and data collection

Patients are visited both preoperatively and intraoperatively. Daily follow − up is conducted during the initial five postoperative days or until discharge, whichever comes first. If patients remain hospitalized for more than 5 days after surgery, an additional visit will be conducted upon hospital discharge. The last day of follow − up is defined as day 90 after surgery. Consequently, patients who are still hospitalized will be contacted for the last time 90 days after their surgery (*see* Table 5 in Appendix 3).

All eligible patients will be informed about the trial and asked for written informed consent before surgery. Sufficient time will be provided to the patients to consider their participation. During the preoperative visit, baseline variables are collected including sex, age, height, weight, functional status (independent, partially independent or totally independent), physical status (according to the American Society of Anesthesiologists score), cardiac status (heart failure, according to the NYHA score, ACS, or persistent ventricular tachyarrhythmias) and smoking status. Data on pulmonary status, COPD (if inhalation therapy and/or systemic steroids are used) and respiratory infection within the last month before surgery will be collected as well. Other collected baseline variables include history of active cancer, history of diabetes mellitus including the use of insulin or oral antidiabetics, type of scheduled surgery, transfusion of blood products within 6 h prior to surgery and vital parameters (SpO_2_ and blood pressure). Blood tests (creatinine, hemoglobin, white blood cell count) and chest imaging (assessed on mono − and bilateral infiltrate, pleural effusion, atelectasis, pneumothorax, and cardiopulmonary edema) are collected solely when deemed necessary for clinical care for the patient.

After induction of anesthesia, variables are collected hourly during the intraoperative period. These variables include ventilator settings, vital parameters, intra-abdominal pressure, administered fluids and vasoactive drugs, blood transfusions, need for rescue strategy for hypoxemia, intraoperative complications possibly related to PEEP titrations, preapproved protocol deviations and violations, details of anesthesia (type, epidural analgesia, neuromuscular function monitoring), patient positioning during surgery, arterial blood gas results (only if deemed necessary for clinical care for the patient), amount of fluid loss, and duration of both surgery and anesthesia procedures. Patients allocated to the individualized high PEEP with RMs group will have their plateau pressure recorded at the end of each decremental PEEP trial step and a ΔP–PEEP graph will be drawn.

Postoperatively, clinical data and the occurrence of pulmonary and extrapulmonary postoperative complications are collected. Blood tests and chest imaging will only be performed when considered necessary for the patients’ clinical care. Life status (death or alive) will be recorded during the first five postoperative days and at day 90 after surgery. Total length of stay in hospital, unplanned admission to an intensive care unit (ICU), and length of stay in the ICU are captured as well. To assess the health − related quality of life, the validated and commonly used EQ − 5D − 5L questionnaire will be sent out by email at day 90 after surgery to Dutch patients.

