### Control group

Patients randomized to the standard low PEEP without RMs group will receive 5 cm H_2_O PEEP for the complete duration of intraoperative ventilation. This specific PEEP level of 5 cm H_2_O has been selected as it represents the most commonly selected PEEP level in daily clinical practice [1, 16]. They will neither undergo the planned RMs nor a decremental PEEP trial.

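### The data-collection text describes a narrower set of intraoperative complications than secondary endpoint (i) and ties it to a procedure planned in one arm only, which risks unequal recording between arms

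*Protocol article*

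**What the plan says.** The protocol article describes intraoperative complications in three places.

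- **Trial endpoints, secondary endpoint (i):** "Intraoperative complications, that are not related to induction or change of the depth of anesthesia". The components are desaturation, hypotension, vasoactive need and new arrhythmia. Anesthesia induction or depth is the only causal exclusion. No link to PEEP is required and no arm is singled out.
- **Trial visits and data collection:** "After induction of anesthesia, variables are collected hourly during the intraoperative period. These variables include ventilator settings, vital parameters, intra-abdominal pressure". The same list continues with "administered fluids and vasoactive drugs, blood transfusions, need for rescue strategy for hypoxemia" and then names "intraoperative complications possibly related to PEEP titrations". This is the only complications item in the list.
- **Table 5 (Appendix 3):** intraoperative complications are marked for the surgery period, with no mention of PEEP and no arm restriction.

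On which arm has the procedure, the section Control group says of control patients: "They will neither undergo the planned RMs nor a decremental PEEP trial". The decremental PEEP trial belongs to the section Intervention. Minimization of bias states that the attending anesthesiologist cannot be blinded.

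**The concern.** The data-collection section adds a condition that neither the endpoint definition nor Table 5 contains. This is a contradiction within the article and not a detail left out by condensation.

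The added condition does not bear equally on the two arms. An episode of hypotension soon after a decremental PEEP trial is easily called possibly related to titration. The same episode in a control patient with unchanged PEEP usually is not. The judgement is made around the operation, where the attending anesthesiologist knows the allocation, and the article does not say who makes it.

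At stake is the between-arm comparison of desaturation, hypotension, vasoactive need and arrhythmia. If control episodes are recorded less completely, the intervention looks more harmful than it is. Under Statistical analysis every outcome is tested two-sided at 5% without multiplicity adjustment, so a recording artefact could be reported as a significant difference.

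**Working it through.** **1. Compare the three descriptions.**

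| Place | Event set | Link to PEEP titration | Arm |
|---|---|---|---|
| Trial endpoints, (i) | any qualifying episode | not required | both |
| Table 5 | intraoperative complications | not mentioned | both |
| Trial visits and data collection | complications possibly related to titration | required | not stated, but planned titration is in one arm |

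The third row is a subset of the first two.

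**2. Ask whether the other collected items restore the missing episodes.**

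- Desaturation and hypotension: vital parameters are collected hourly, while the endpoint needs an episode of more than 1 minute. Hourly values do not reliably show an episode just over that length. Need for hypoxemia rescue is not the same event as any desaturation of more than 1 minute.
- Vasoactive agents: the endpoint is "Any need for vasoactive agents, either as bolus or continuous administration", limited to use beyond what offsets anesthetic vasodilation. Drugs administered do not by themselves show that excess.
- Arrhythmia: the list has no separate item. Preapproved deviations cover only new arrhythmias that do not respond to guideline treatment.

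The cover is therefore partial.

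**3. Reproduce the plan's sample size, which supplies n for the illustration.** Inputs from Sample size calculation and Statistical analysis: 30% v 24%, two-sided alpha 0.05, power 80%, 1:1. With pooled variance and no continuity correction:

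n = [1.960 × √(2 × 0.27 × 0.73) + 0.842 × √(0.30 × 0.70 + 0.24 × 0.76)]² / 0.06² ≈ 859 per group.

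The plan states 860, at which power is 0.801. It is reproduced, and this point does not change it.

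**4. Illustrate the effect of unequal capture.** The article gives no complication rate and no capture rate, so these are assumptions: 860 per arm, the same true rate p in both arms, full capture in the intervention arm, and capture c in the control arm. The recorded control rate is q = pc and the spurious difference is d = p(1 − c). With p̄ = (p + q)/2,

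SE₀ = √[2p̄(1 − p̄)/860], SE₁ = √{[p(1 − p) + q(1 − q)]/860},

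P(significant) = Φ[(d − 1.96 SE₀)/SE₁] + Φ[(−d − 1.96 SE₀)/SE₁].

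For p = 0.30 and c = 0.90: q = 0.27, d = 0.03, SE₀ = 0.02177, SE₁ = 0.02176. The first term is Φ(−0.58) ≈ 0.280 and the second is below 0.001, giving 0.281.

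| True rate | c = 1 | c = 0.95 | c = 0.90 | c = 0.80 |
|---|---|---|---|---|
| 10% | 0.050 | 0.064 | 0.109 | 0.305 |
| 20% | 0.050 | 0.082 | 0.185 | 0.579 |
| 30% | 0.050 | 0.105 | 0.281 | 0.801 |
| 40% | 0.050 | 0.136 | 0.401 | 0.933 |

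The spurious difference at c = 0.90 is 1 point at a true rate of 10% and 3 points at 30%.

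**The case against.** A reader might infer that the trial records only titration-related complications, so that control-arm events are missed by design and fall near zero. The documents do not support this, for four reasons.

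- The list is open: it says what the variables include and never says that nothing else is recorded. Where one arm alone is meant, as for plateau pressure during the PEEP trial, the same section says so.
- Table 5 carries the item unqualified, in agreement with endpoint (i).
- PEEP changes are not absent from the control arm. Table 3 describes raising PEEP and a recruitment maneuver as rescue there, and the preapproved deviations, introduced for both groups, mention the period after PEEP titration. A control episode can therefore qualify.
- Vital parameters, vasoactive drugs and hypoxemia rescue are collected without the qualifier, and Handling of data says that data come from the electronic patient record.

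It is also fair to say that the case report form is not shown and may already collect every episode, and that the false-positive figures rest on assumed rates. Full capture in the intervention arm is a simplification too, since the qualifier could drop unrelated episodes there.

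All of this stands against the strong reading, and a scenario with no control episodes recorded should not be used. The mismatch in wording remains. Control rescue reaches PEEP only after desaturation and several steps of inspired oxygen, so a control patient's first episode would rarely meet the qualifier. The unqualified items do not fully replace an episode record.

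**Conclusion.** The point holds as an internal contradiction that carries a risk of differential recording; it does not establish that under-recording occurs. The data-collection wording is narrower than secondary endpoint (i) and Table 5, and its qualifier refers to a procedure planned in one arm. If staff follow it, the likely direction of bias is against the intervention.

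The size cannot be derived from the documents. Under the assumptions stated in the check, a loss of one control episode in ten would roughly double the 5% error rate at a true rate of 10% and take it to more than five times the nominal level at 30%. A modest gap would therefore matter. The consequence is confined to this secondary endpoint; the primary endpoint and its sample size are not touched. The change should be made, because it removes the risk at little cost.

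**What to change.** In Trial visits and data collection, replace the qualified item with wording to this effect: *all intraoperative complications that meet secondary endpoint (i), recorded in both groups irrespective of any presumed relation to PEEP titration*. Change the case report form item in the same way if it carries the same qualifier. If relatedness is of interest, keep it as a separate descriptive field that does not decide whether an episode counts.

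The cost is one sentence, possibly one form instruction, and some additional data entry. Recruitment began in December 2023, so patients already enrolled may need a check of their anesthesia records. If the form already collects every qualifying episode, correcting the sentence is enough. No clinical rule changes.
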